## General study methodology

The study presents the following characteristics:

- ***Phase 2a and 2b study to evaluate the safety and efficacy of XAV-19***
- ***Both phases are multicenter, placebo-controlled, double-blind, randomized***
- ***Phase 2a is a sequential 2 groups ascending dose, with a 1:1 randomisation for the first two patients and a 5:1 ratio (treatment: placebo) for the 6 following patients). Subjects will be dosed with a minimal interval of 24h (first to first administration) all sites combined.***
- ***Phase 2b is a double-blinded 1:1 randomised study with randomisation balanced by blocks. A randomisation by center and by duration between onset of COVID-19 symptoms and screening (1-6 days, 7-10, 11 to 14 days) will be settled****.*
- To note, the terminal ancillary study of phase 2b will be performed as open label.

## Study diagram

### Phase 2a – Group1

Adults patients with moderate COVID-19 confirmed by RT-PCR

Inclusion visit: verification of eligibility criteria and signature of informed consent form

Follow-up visits until day 29 and phone call at Day 60

**Experimental Group 1**

XAV-19 at 0,5mg/kg

Administration at Day 1 and Day 5

6 patients

Randomisation 5:1 (treatment : placebo)

2 patients

Randomisation 1:1 (treatment : placebo)

Stop

1st XAV-19 Administration Day1

1st XAV-19 Administration Day1

**Safety Data Review**

**&**

**Evaluation by DSMC**

2nd XAV-19 Administration Day5

2nd XAV-19 Administration Day5

Follow-up Visits until Day29 and phone call at Day 60

Follow-up Visits until Day29

and phone call at Day 60

**DSMC**

**Evaluation of data until Day 8 for the 8 patients**

**GROUP2**

**STOP**

Stop

### Phase 2a - Group2

Adults patients with moderate COVID-19 confirmed by RT-PCR

Follow-up visits until day 29 and phone call at Day 60

Inclusion visit: verification of eligibility criteria and signature of informed consent form

**Experimental Group 2**

XAV-19 at 2mg/kg

Administration at Day 1 and Day 5

6 patients

Randomisation 5:1 (treatment : placebo)

2 patients

Randomisation 1:1 (treatment : placebo)

Stop

1st XAV-19 Administration Day1

1st XAV-19 Administration Day1

**Safety Data Review**

**&**

**Evaluation by DSMC**

2nd XAV-19

Administration Day5

Follow-up Visits until Day29 and phone call at Day 60

Follow-up Visits until Day29

and phone call at Day 60

**Phase 2b**

**STOP**

Stop

**DSMC**

**Evaluation of data until Day 8 for the 8 patients**

### Phase 2b

398 Adults patients with moderate COVID-19 confirmed by RT-PCR + 20 patients (terminal ancillary study)

D0: Inclusion visit: verification of eligibility criteria and signature of informed consent form

Follow-up visits until day 29 and phone call at Day 60

D1: Randomisation 1:1 (treatment:placebo) only for the first 398 patients

1st XAV-19 Administration Day1

(fixed dose of 150mg for the 20 patients of the terminal ancillary study)

Follow-up visits until Day 29 and phone call at Day 60

Follow-up visits until Day 29

Follow-up visits until Day 29

Follow-up visits until Day 29

## Identification of all data sources not included in the medical record

All specific data from the study will be compiled directly in the eCRF, as they will not be found in medical record.

These specific data are:

- Urinary pregnancy test at D1

- 12-Lead ECG at D1

- Immunological analysis

- Spike/ACE2 interaction neutralizing antibody
- Cytokines
- Lymphocytes sub-population
- Transcriptomic analyses

- PK analysis

- The 7-point Ordinal Scale or the 8-point Ordinal Scale

All other data will be present in the patient medical file.

## Rules for discontinuing subject participation

### Criteria in respect of early withdrawal of a subject from the study

Withdrawals from the study can only be effective after confirmation by the investigator and the sponsor. These withdrawals are always definitive

Patients can withdraw from participation in this study at any time, for any reason, specified or unspecified, and without prejudice.

Criteria in respect of early withdrawal of a subject from the study are the following:

- Withdrawal of informed consent (subject’s decision to withdraw for any reason). All data gathered before their withdrawal will be kept for analysis
- Investigator’s decision to stop the study in the patient’s best interest. Patients who stop prematurely or definitively the study treatment will be kept in the study for follow-up
- Subjects who have grade 4 reaction secondary to first XAV-19 administration and/or develop serum sickness disease, serious allergic reaction such as anaphylactic shock, severe hypotension, tachycardia or Quincke’s edema following first XAV-19 administration will discontinue study treatment but will be kept in the study to perform the required study-related follow-up and procedures
- For the phase 2a, subjects who discontinue prior to the Day 8 in phase 2a will be replaced, in order to obtain the required number of evaluable subjects in each group (8 patients). There will be no replacement of discontinued patients in phase 2b.
- Termination of the study by the Sponsor

Stopping rules:

| **Parameter** | **Value** |
| --- | --- |
| Adverse events | Grade 4 reaction secondary to first XAV-19 administration and/or develop serum sickness disease, serious allergic reaction such as anaphylactic shock, severe hypotension, tachycardia or Quincke’s edema |
| **Vital signs** |  |
| - Bradycardia | - <50 beats/min or ECG abnormalities |
| - Tachycardia | - >130 beats/min or ventricular dysrhythmias |
| Supine systolic blood pressure increase | >200 mmHg or headache or clinical signs |
| Supine diastolic blood pressure increase | >120 mmHg or headache or clinical signs |
| Supine systolic blood pressure decrease | <70 mmHg or symptomatic |

Every effort should be made to keep the patients in the trial, if possible, on treatment, or at least post-treatment discontinuation to collect important trial data.

For the data processing procedures in respect of subjects withdrawn early from the study, refer to the statistical section.

### Procedures in respect of early withdrawal of a subject from the study

In the event of early discontinuation of the study treatment, all efforts will be made by the investigator to invite the patient to undergo the end of study (EOS) visit.

The primary reason for discontinuation must be recorded in the appropriate section of the e-CRF and all efforts made to complete and report the observations as thoroughly as possible. A complete final evaluation following the patient's withdrawal should be made, as described in Section 6.1.8 (Early Withdrawal Visit).

If a patient fails to return for a scheduled visit/follow up, attempts should be made to contact the patient to identify reason for not returning. Likewise, if a patient declares his/her wish to discontinue from the study e.g., for personal reasons, all efforts should be made to establish that the cause is not due to an AE (bearing in mind the patient is not obliged to state his/her reasons).

For the data processing procedures in respect of subjects withdrawn early from the study, refer to the statistical section.

Each early departure from the study should receive the usual medical follow‐up.

### Criteria in respect of discontinuation of all or part of the study (excluding biostatistical considerations)

The first part of the study (phase 2a) as a first-in-human study is conducted with sequential enrolment to check for safety.

The DSMC will give recommendation regarding modification to the ongoing conduct of the trial (see 1.2.4) and give approval for continuing the study to the next step within each group of phase 2a and between the phase 2a and 2b.

At any time during the phase 2a study, if a serious adverse event occurs, this will be communicated to the DSMC, and the sponsor and coordinating investigator will have the responsibility to decide whether DSMC must meet to advise on study conduct. The DSMC may also be requested for a review by the person in charge of safety pharmacology if a SUSAR or a SAE presents a particular analytical problem or if a doubt in respect benefit/risk arises during the study and advise on study conduct.

Due to the small number of patients and the short duration of follow-up, no further rules for early termination of research are defined for phase 2a.

During the main phase of the study (phase 2b), the DSMC will regularly meets as defined in the DSMC charter and may decide to stop the study prematurely.

During the phase 2b study, if the proportion of patients with need of invasive mechanical ventilation and/or death after inclusion reaches to 20% or above (analyzed by incremental groups of 50 patients), the DSMC will be asked to review the data without stopping the study (see 6.6.3). If the proportion of patients dead and/or requiring post-enrolment invasive mechanical ventilation after inclusion reaches 35% of above of the patients included in the study (analyzed by incremental groups of 50 patients), the enrolments will be temporarily discontinued and DSMC will be asked to review the data and decide on an early permanent discontinuation of the study (see 6.6.3).

References:

- study ACTT-1 (Beigel JH. NEJM 2020; 383:1813-26)

- study GS-US-5773 (Goldman JD. NEJM 2020; 383:1827-37)

- study CORIMUNO-TOCI (Hermine O. JAMA Intern Med 2020; Oct 20 (online ahead of print)

The number of patients requiring mechanical ventilation after inclusion will be tracked over time.

The thresholds requiring DSMC intervention or premature discontinuation of the study have been defined in incremental groups of 50 patients as follows:

| Number of patients included | Number of patients requiring invasive mechanical ventilation after inclusion | |
| --- | --- | --- |
|  | For DSMC intervention | For temporary discontinuation of the study |
| Up to 50 | 10 | 18 |
| 51 to 100 | 20 | 35 |
| 101 to 150 | 30 | 53 |
| 151 to 200 | 40 | 70 |
| 201 to 250 | 50 | 88 |
| 251 to 300 | 60 | 105 |
| 301 to 352 | 70 | 124 |
| 353 to 398 | 80 | 140 |

These criteria applied to this day may need to be modified according to the evolution of the epidemic.

A definitive or temporary discontinuation of all or part of the study may be decided by ANSM, the Ethics Committee, the Sponsor after Data and Safety Monitoring Committee (DSMC) opinion*.*

In any case:

- A written confirmation of this early discontinuation of the study shall be sent to the coordinating investigator of the study (specifying the reasons for the early discontinuation),

- All the patients included in the study shall be informed and should attend their early withdrawal visit.

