## Safety evaluation parameters

### Specific safety-related evaluation criteria

All patients will be closely monitored during both study phases for overall biological and clinical safety data (eg. infections or malignancies) and any drugs toxicity.

According to regulation, each AE/AR reported by the patient or identified by the investigator must be collected and reported to sponsor, as soon as he is aware, if it meets to seriousness criteria from inclusion of the subject, to the end of the participation.

As a precaution, patients enrolled in this trial must be observed during infusion of study drug and for at least 2 hours post infusion. Patients will be assessed for signs or symptoms of any infusion reactions (e.g., hypotension, hypoxia, tachycardia, fever, nausea, fatigue, headache, myalgia, and malaise).

The safety assessment in this study will be based on physical examination, vital signs, AEs, clinical laboratory tests and other biological tests and ECG, as described in the sections 5.2 (Procedure Details).

New symptoms suspected to be related to COVID-19/SARS-CoV-2 infection that start after the initiation of study treatment should be reported as AEs.

Worsening of symptoms related to COVID-19/SARS-CoV-2 infection should be closely medically analyzed, and should be reported as AE if, the symptoms are clinically significant and/or lead to treatment modification :

- For instance, in case of increase of oxygen requirement, investigators, taking into account the full clinical situation, will judge whether this increase in O2 treatment is related to a clinically significant complication or worsening that shall then be considered as either an AE or notified as a SAE

- In case of transfer to ICU, investigators will consider the reason responsible for this patient's management (worsening of COVID-19/SARS-CoV-2 infection, concomitant disease, or only local logistical management) to decide if AE or SAE must be considered. Clinically significant symptoms without acute severity criteria (e.g., transfer to the intensive care unit for close monitoring, including optiflow or NIV requirement) should be considered AE.

New symptoms leading to a risk of short-term mortality due to their severity should be reported as SAE, e.g. mechanical ventilation or high-flow oxygen therapy for patients in whom mechanical ventilation is not considered for ethical reasons.

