## Randomization will be double-blinded and balanced by blocks.Stopping guidance - Critical COVID and death follow-up

During the phase 2b study, the DSMC will regularly meets as defined in the DSMC charter and may decide to stop the study prematurely.

Three meetings will be scheduled after the inclusion of D29 of the 50^th^, 150^th^ and 300^th^ patient. Rates of invasive mechanical ventilation and death will be presented and any other information asked by the DSMC.

If the proportion of patients with need of invasive mechanical ventilation and/or death after inclusion reaches to 20% or above (analyzed by incremental groups of 50 patients), the DSMC will be asked to review the data without stopping the study.

If the proportion of patients dead and/or requiring post-enrolment invasive mechanical ventilation after inclusion reaches 35% of above of the patients included in the study (analyzed by incremental groups of 50 patients), the enrolments will be temporarily discontinued and DSMC will be asked to review the data and decide on an early permanent discontinuation of the study.

References:

- study ACTT-1 (Beigel JH. NEJM 2020; 383:1813-26)

- study GS-US-5773 (Goldman JD. NEJM 2020; 383:1827-37)

- study CORIMUNO-TOCI (Hermine O. JAMA Intern Med 2020; Oct 20 (online ahead of print)

The number of patients requiring mechanical ventilation after inclusion will be tracked over time.

The thresholds requiring DSMC intervention or premature discontinuation of the study have been defined in incremental groups of 50 patients as follows

| Number of patients included | Number of patients requiring invasive mechanical ventilation after inclusion (after randomization) | |
| --- | --- | --- |
|  | For DSMC intervention | For temporary discontinuation of the study |
| Up to 50 | 10 | 18 |
| 51 to 100 | 20 | 35 |
| 101 to 150 | 30 | 53 |
| 151 to 200 | 40 | 70 |
| 201 to 250 | 50 | 88 |
| 251 to 300 | 60 | 105 |
| 301 to 352 | 70 | 124 |
| 353 to 398 | 80 | 140 |

These criteria applied to this day may need to be modified according to the evolution of the epidemic.

A definitive or temporary discontinuation of all or part of the study may be decided by ANSM, the Ethics Committee, the Sponsor after Data and Safety Monitoring Committee (DSMC) opinion.

In any case:

- A written confirmation of this early discontinuation of the study shall be sent to the coordinating investigator of the study (specifying the reasons for the early discontinuation),

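### The Phase 2b stopping rule is stated on ventilation and/or death, but its threshold tables and tracking sentence name only ventilated patients

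*Combined protocol and SAP*

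**What the plan says.** Protocol 6.7.3 states the review trigger as applying "if the proportion of patients with need of invasive mechanical ventilation and/or death after inclusion reaches to 20% or above", and the pause trigger as "If the proportion of patients dead and/or requiring post-enrolment invasive mechanical ventilation after inclusion reaches 35% of above of the patients included in the study". Both are assessed in steps of 50 patients. Protocol 1.2.4 and SAP 2.5 (Stopping guidance) give the same two triggers with the same event.

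Both documents then move to counts. The lead-in sentence is "The number of patients requiring mechanical ventilation after inclusion will be tracked over time". The column heading in the protocol table is "Number of patients requiring invasive mechanical ventilation after inclusion". The SAP table has the same counts and differs only by a bracketed remark: "Number of patients requiring invasive mechanical ventilation after inclusion (after randomization". Death appears in neither table heading and not in the tracking sentence. The table is introduced as the definition of the thresholds for DSMC intervention and discontinuation, so it is not presented as a second, separate rule.

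**The concern.** A stopping threshold should give one answer. Here, someone working from the paragraph counts every patient who dies or is ventilated, and someone working from the table counts only the ventilated. When some patients die without ventilation, the two can disagree on whether the DSMC is called or enrolment is paused.

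Such deaths are foreseeable in this trial. Protocol 8.2.1 gives, as an example of an event to report as serious, "high-flow oxygen therapy for patients in whom mechanical ventilation is not considered for ethical reasons". Phase 2b also has no upper age limit, whereas Phase 2a stops at 85 years.

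**Working it through.** **1. Reproduce the tables.** Inputs: the 20% and 35% triggers and the upper limit n of each band (Protocol 6.7.3, SAP 2.5). Formula: 0.20 × n and 0.35 × n, rounded up.

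| n | 0.20 × n | Table | 0.35 × n | Table |
|---|---|---|---|---|
| 50 | 10 | 10 | 17.5 → 18 | 18 |
| 100 | 20 | 20 | 35 | 35 |
| 150 | 30 | 30 | 52.5 → 53 | 53 |
| 200 | 40 | 40 | 70 | 70 |
| 250 | 50 | 50 | 87.5 → 88 | 88 |
| 300 | 60 | 60 | 105 | 105 |
| 352 | 70.4 → 71 | 70 | 123.2 → 124 | 124 |
| 398 | 79.6 → 80 | 80 | 139.3 → 140 | 140 |

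Fifteen of the 16 counts match. The exception is in the row "301 to 352 | 70 | 124", where 70/352 = 19.9%. The table therefore carries the percentages of the rule text. The arithmetic does not show which event was intended, because the counts would be the same under either label.

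**2. Effect of the narrower event.** Let d be the share of ventilation-or-death events that are deaths without ventilation. The documents do not give d, so it is assumed. A ventilation-only count reaches a threshold t when the true ventilation-or-death rate is t / (1 − d).

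| Assumed d | 20% count reached at | 35% count reached at |
|---|---|---|
| 10% | 0.20/0.90 = 22.2% | 0.35/0.90 = 38.9% |
| 25% | 0.20/0.75 = 26.7% | 0.35/0.75 = 46.7% |
| 30% | 0.20/0.70 = 28.6% | 0.35/0.70 = 50.0% |
| 50% | 0.20/0.50 = 40.0% | 0.35/0.50 = 70.0% |

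For example, take 200 patients and d = 30%. Seventy events are 49 ventilated patients (0.70 × 70) and 21 deaths without ventilation. The text pauses enrolment, since 70/200 = 35%. The table shows 49, which is above its review count of 40 but below its pause count of 70.

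**3. Chance of triggering review.** Simulation: 40,000 trials, 1:1 allocation, eight looks at the band limits, outcomes assumed known at once. With assumed ventilation-or-death rates of 15% on placebo and 30% on XAV-19, the review count is reached at some look in 97% of trials if all events count, in 45% if d = 25%, and in 5% if d = 50%.

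**4. What a pooled trigger can show.** The denominator is all patients included, with no count by arm. The same simulation, counting all events, gives:

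| Placebo vs XAV-19 (assumed) | Ever review | Ever pause |
|---|---|---|
| 5% vs 10% | 0.3% | 0% |
| 10% vs 20% | 25% | 0.01% |
| 15% vs 15% | 26% | 0.01% |
| 10% vs 30% | 83% | 0.4% |
| 15% vs 30% | 97% | 2% |
| 20% vs 40% | 100% | 30% |

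The second and third rows both pool to 15% and raise review about equally often. The trigger follows the overall rate and not the difference between arms.

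**The case against.** The strongest reply is that the rule is written out in three places with death included, so the table has merely an incomplete label that a sensible reader would complete. SAP 2.5 supports this: ventilation and death rates are both to be presented at DSMC meetings tied to Day 29 of the 50th, 150th and 300th patient, with anything else the DSMC requests. The DSMC may stop the study outside the table, and serious events can prompt a review (Protocol 6.7.3, 8.4.5). Excluding patients with a life expectancy under six months also limits the group in whom ventilation would not be considered.

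Much of this stands. A reader might infer that deaths without ventilation are definitely left out of monitoring. The documents do not support that: the rule text counts them and the DSMC sees them. But the reply does not remove the contradiction. The tracking sentence and two table headings agree with each other against the text, and the table is the form in which the rule would be applied between meetings.

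A reader might also infer that the pooled trigger can barely detect harm on XAV-19. That is too general: counting all events, review fires in 83% of trials at 10% vs 30% and 97% at 15% vs 30%. Nor do the documents show that the DSMC is denied results by arm. They are silent, and the DSMC charter is not among them. A between-arm harm boundary is a design preference, not a correction.

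**Conclusion.** Wrong as written, in both documents: one stopping rule has two event definitions, and the answer depends on which part is followed. The size depends on the share of events that are deaths without ventilation, which the documents do not give. At an assumed 10% to 30%, the nominal 20% trigger acts at a true 22% to 29%, and the nominal 35% trigger at 39% to 50%, if the table is followed literally. If the text is followed, there is no shift.

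Pooling is a limit to note and not an error. The pause trigger rarely fires for a doubling of risk at placebo rates up to 15% (at most about 2% of trials), and no pooled count can attribute a high rate to an arm. The scheduled meetings and the DSMC's power to stop partly cover this. The underlying event rates are assumptions, and the simulations ignore outcome delay, which would lower the chance of triggering further.

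**What to change.** Reconcile the rule text (Protocol 1.2.4 and 6.7.3, SAP 2.5), the tracking sentence and the column headings of both tables to one stated event definition, and say that each patient is counted once. The sponsor should state which event is meant. The same edit can confirm or correct the 70 at 352 patients and the references to 6.6.3, since the rule stands in 6.7.3. The cost is wording only: sample size, primary analysis and blinding are untouched.

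Two additions that may suggest themselves should not be made in this edit:

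- Restricting the denominator to patients who have reached Day 15 or had an earlier event biases the rate upward, because recent patients with events stay in and recent patients without events drop out. Assume 100 inclusions per month, events spread evenly over 15 days and a true rate of 15%. At the 100th inclusion, 50 patients have full follow-up with 7.5 events, and the other 50 have shown 3.75 events. The rate reads (7.5 + 3.75)/(50 + 3.75) = 21%.
- An unadjusted between-arm confidence limit checked at all eight steps would have no stated false-alarm rate.

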## Patient medical care at the end of the study

After the end of the study, each patient will receive the usual medical follow‐up.

# Data Management AND STATISTICS

## Data entry and data collection

### Data entry, processing and circulation

An electronic data capture system, eCRF, will be used for data collection in this study.

Each person (investigator, CRT, Project Manager, CRA) has a personal user account in connection with their role (profile) that has been assigned to them by the trial sponsor. The creation and administration of computer accounts are managed by the Data Manager in charge of the test.

Each user must change their initial password on first login, using an encrypted password of at least 8 alphanumeric characters, valid for 30 days. The system will revert to standby after 15 minutes of inactivity on the application, and users will be blocked after three unsuccessful login attempts. Each person will be trained for the use of the eCRF

Data collection will be done directly by the investigator or CRA in charge of the study, using an eCRF accessible since the web site <https://nantes-lrsy.hugo-online.fr/EnnovClinical> and developed by the Promotion Department of the University Hospital of Nantes with Ennov Clinical software.

The eCRF is designed to record the data required by the protocol and collected by the investigator. The investigator must ensure that data are recorded and any corrections in the eCRF are made as stated in the study protocol and in accordance with the instructions. The investigator must ensure that the recorded data is correct, complete, and that reporting takes place according to the timelines that have been predefined and agreed. The investigator signs the completed eCRF.

